### Initial contact with potential participants

For all the women who agreed for participation, information will be collected on demographic profile (age, education, religion, caste, occupation, family type, per capita income etc.); reproductive phase with respect to age at marriage, occurrence of live birth, place of delivery, number of antenatal care and post-natal visits, post-natal complications, if any etc. Participants will undertake USG dating scans (ideally before 14 weeks of pregnancy) and baseline obstetric history and demographic data will be obtained. They will also be informed that during a subsequent visit they would be requested to provide saliva sample between 24 and 28 weeks of pregnancy, and that they will be followed-up in the postnatal period to obtain birth outcomes.

Each pregnant woman recruited in the study will be provided a Unique ID at the time of registration. Link anonymised data will be entered onto a study specific internet-based database (MedSciNet https://promises.medscinet.com/). The database is password protected and will have different level of users (i.e. unit users, monitoring users and global administrators).

### Arranging the first household visit

The first household visit will include consent and recruitment of the pregnant women for the study. This will also include briefing of the women about the importance of the study and the negative outcomes for mother and baby relating to preterm birth. Inclusion/exclusion criteria will be checked thoroughly. Any queries from the participants will be addressed.

### Antenatal care (ANC) visit (for ultrasonography)

Recruited pregnant women will be taken to an identified government hospital facilities or private facility for ultrasound dating of pregnancy. The radiologist at this facility will record fetal measurements and preserve data the frozen scan frames (anonymised labelled with study ID and date only). A consultant radiologist at MGIMS will provide field-based training and randomly check data/images as a second verification step to determine agreed estimated date of delivery. Anticipating that at scan, a proportion of pregnancies will be found to be > 14 weeks, a range of fetal measurements will be taken (crown-rump length, bi-parietal diameter; head circumference; abdominal circumference or diameter to include second trimester scans [31].

### Visit for sample collection

A further visit to participants by outreach workers to collect the saliva sample will occur between 24 and 28 weeks of gestation of the participants. At this stage, an additional informed consent will be gained.

### Sample collection procedure

Women will be encouraged to provide saliva sample after an overnight fasting. Sample collection within 60 min after eating a major meal or within 12 h after consuming alcohol will be strictly avoided. Acidic or high sugar foods can compromise assay performance by lowering sample pH and influencing bacterial growth. To minimize these factors, participants will be asked to rinse mouth thoroughly with water 10 min before sample is collected. Saliva will be collected by the passive drool method into a small. The start time will be noted, and a sample of at least 5 ml of saliva will be collected into graduated labelled polypropylene container over approximately 5–10 min and then placed into ice. Saliva samples visibly contaminated with blood will be discarded and recollected where possible within the 7 days.

### Sample transportation and storage

The unique Patient ID will be used (along with other time and date information) to track sample collection and storage. Samples will be stored at the district field office at − 20 °C until dispatched to the MGIMS laboratory. The time of saliva collection and the time at which samples reached freezer is noted at this time. These data along with bar coded tube information will be entered into the participant’s electronic record form on the database.

#### I. Transportation from study site to field office

Although progesterone is relatively stable, due to the high temperature that can be experienced at the study site, after collection of the saliva sample from a participant, it will immediately be placed inside the ice box. The samples will be transferred within 30 min to district field office. All the samples in district office will be kept in − 20 °C.

#### II. Transportation from field office to MGMIS laboratory

Frozen samples will be transferred using cold (4 °C) transportation carriers and will be sent to the MGMIS laboratory for progesterone ELISA analysis in batches. The district coordinators will undertake the activity to avoid loss of samples during transition. This approach includes a planned freeze-thaw cycle to ensure that samples will arrive cold (temperature monitored on arrival; thawed samples will be divided into two aliquots (barcode labelled) for storage at − 80 °C and future analysis of progesterone by ELISA (Demeditec Diagnostics GmbH, CAT No. DES 6633).

### Follow up visit

The recruited participants of the study will be visited to collect information about pregnancy outcome (e.g. time and date of delivery, gestation at delivery, medications received and total inpatient nights) and neonatal outcome (e.g. male or female, live/dead, birth weight, congenital abnormality, any neonatal complications and date of discharge). Additional/missing details of any pregnancy complications will be tracked through their registered antenatal care visits cards.

### Exit from the study

The delivery outcome information will be obtained during the final visit by ORWs from all the registered women in the study (i.e. also including women who did not get a USG, were outside the study gestation window, or did not provide saliva).

### Data management

A data safety monitoring board (DSMB), responsible for data management, reporting, protocol sharing and regular reviews, was convened with members from the three collaborating institutions (MGIMS, MAMTA and Kings College London).

### Study outcomes

Three major outcomes will be determined.

i. The association between salivary progesterone at 24–28 weeks of pregnancy and PTB.

ii. Performance of salivary progesterone test (sensitivity, specificity, predictive values and ROC areas) will be produced for different cut-off values of salivary progesterone for prediction of PTB (< 34 and < 37 weeks of gestation).

iii. Evidence of feasibility and acceptability of this low cost innovation for early identification of pregnant women in rural low resource setting.

For preterm birth, the primary endpoint will be spontaneous preterm birth or PPROM < 34 weeks and secondary endpoints < 37 weeks of pregnancy, < 30 weeks. Additional secondary endpoints will include gestation at delivery and a range of maternal and neonatal outcomes (composite and individual.

A qualitative approach will be used to determine the acceptability of the salivary progesterone test to pregnant women and frontline functionaries (qualitative interviews).

### Sample size and data analysis

A significant difference between cases of PTB and controls is not sufficient to show that a test is clinically useful. Both sensitivity and specificity must be evaluated. Accurately determining the sensitivity is harder (due to smaller numbers), and the sample size determination accordingly concentrates on this. Based on the PTB rates in two study districts (~ 23%), recruitment of 2000 women would potentially identify 460 preterm deliveries at < 37 weeks’ providing ample power to predict PTB at this gestation and to use data for discovery and validation. Data from Lachelin et al., [19] indicates the salivary progesterone test works best to detect birth < 34 weeks, but this incidence for this gestation is not known for the study districts. However, if 189 cases of PTB < 34 weeks’ are identified (9.5% incidence), this would provide 90% power to distinguish 80% from 70% sensitivity. Calculations were carried out in Stata version 13.1 using the command ‘sampsi’ (StataCorp, College Station, Texas).

At study completion, data will be downloaded into a statistical package in the statistical package Stata, version 15 or later, (StataCorp) and additional data cleaning checks applied. Clinical and pregnancy outcome data will be described for the whole cohort.

Additional predefined exclusion criteria relating to sample availability and contamination, and pregnancy outcome (e.g. iatrogenic PTB, maternal medications such as antidepressants and progesterone, use of cervical cerclage or Arabin pessary).

The data will be randomly split into training and validation sets, each containing the same number of cases (premature deliveries before 37 and 34 weeks) and controls (term deliveries). The training set will be used to determine the best cut-offs to use for a rule-in and a rule-out test. Based on Priya et al., [26], a limited number of simple cut-offs will be investigated: 500, 1000, 1500, 2000, 2500, 3000 pg/ml. These results will define two thresholds, allowing women to be triaged into three groups: “green” (salivary progesterone above the upper threshold), “amber” (progesterone between the two thresholds) and “red” (progesterone below the lower threshold). It is envisaged that if the test proves suitable for general use, the “green” group will receive usual care; the “amber” group will receive more intense advice about meaning of dating scan, due date, etc.; and the “red” group will be advised to change their birthing plan to include delivery in a district tertiary healthcare centre with a neonatal intensive care facility. Following STARD guidelines [32] for diagnostic tests, measures of test performance (sensitivity, specificity, predictive values and ROC areas) will be produced with 95% confidence intervals for the two cut-offs selected as predictors of the primary endpoint: PTB < 34 weeks of gestation, the secondary endpoints: PTB < 37 weeks’ and < 30 weeks’, and other important outcomes: perinatal and maternal and neonatal death and associated morbidities.

Qualitative data will be analysed following COREQ [33] standards. All the qualitative data collected through in-depth interviews will be translated into English transcripts. The analysis of the transcripts will be done using inductive approach. Themes will be identified during the review of the transcripts manually and further these themes will be grouped into key categories.

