## Background

The 2012 Global Action Report on Preterm Birth (PTB) estimates that 15 million PTBs occur annually and that one million neonatal deaths result from prematurity related causes each year [1]. There are 12.9 million premature births annually worldwide [2]. Approximately, over 60% of preterm births occur in in Sub-Saharan Africa and south Asia. PTB, especially early PTB (< 34 weeks of gestation) [3], is a major cause of neonatal mortality and contributes to 75% of neonatal morbidity and 70% of neonatal mortality in industrialized countries [4]. In children under five, preterm birth is the second largest direct cause of child deaths [3]. Preterm babies, in addition to being at a higher risk of neonatal mortality, are at an increased risk of post-neonatal mortality, stunting, and long-term neuro-developmental impairment during childhood. For babies who survive, there is an increased risk of disability, which exacts a heavy load on families and health systems [5]. An estimated 70% of PTBs results from idiopathic preterm labour or pre-labour rupture of membranes and the remainder are iatrogenic because of obstetric or medical indications [6]. PTB has high economic and social burden in terms of health care needs, emotional stress on family in case of preterm baby death and hospital stay [7] (WHO 2012). India has the highest number of PTBs and preterm deaths worldwide [5], contributing to 25% of the overall global preterm related death; of a total 27 million babies born annually, 3.6 million babies are born preterm, and over 300,000 of these preterm babies die each year because of associated complications [5, 8]. This is even more challenging in Indian rural setting where most women are unaware of the risk of PTB; and do not readily access available care and support. This leads to increased maternal and neonatal morbidity and mortality in rural India [9]. A systematic analysis of global, regional and national causes of child mortality in 2013 identified PTB birth complications and infections to be the two major causes of neonatal deaths in India [10]. In addition, surviving preterm babies are at greater risk for short-term health complications including acute respiratory, gastrointestinal, infectious, central nervous system, hearing, and vision problems, and long- term neuro-developmental disabilities such as cerebral palsy, impaired learning and visual disorders, as well as chronic diseases in adulthood [11, 12].

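### The 9.5% incidence beside the 90% power claim is taken over all 2000 recruits and would not yield 189 evaluable primary-endpoint cases

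*Protocol article*

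**What the plan says.** The section Sample size and data analysis (Protocol article) first gives the expected number of births before 37 weeks: "Based on the PTB rates in two study districts (~ 23"%), it says, "recruitment of 2000 women would potentially identify 460 preterm deliveries at < 37" weeks. For births before 34 weeks it admits that "this incidence for this gestation is not known for the study districts", and then makes a conditional statement: "if 189 cases of PTB < 34 weeks" are found, "9.5% incidence), this would provide 90% power to distinguish 80% from 70% sensitivity". The Study design section makes the same claim.

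Other sections fix who counts as a case and who can be analysed:

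- Study outcomes: "the primary endpoint will be spontaneous preterm birth or PPROM" before 34 weeks.
- Sample size and data analysis: predefined exclusions cover sample availability and contamination, iatrogenic preterm birth, certain medications, cerclage and pessary.
- Background: "An estimated 70% of PTBs results from idiopathic preterm labour or pre-labour rupture of membranes and the remainder are iatrogenic".
- The sections on the first household visit, the ultrasound visit and the sample visit: consent comes first, the dating scan follows, and saliva is collected later under a second consent.
- Inclusion & Exclusion criteria: women dated only by last menstrual period, and women who give no saliva, stay in for clinical data.
- Exit from the study: outcomes are collected from all registered women, "also including women who did not get a USG, were outside the study gestation window, or did not provide saliva".

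**The concern.** The sample size rests on sensitivity, so the number that matters is the count of primary-endpoint cases with a usable dating scan and a usable progesterone result. The article translates the required 189 into an incidence by dividing by everyone recruited. Its own endpoint definition and exclusions then remove some of those births and some of those women, and no allowance for this appears beside the figure.

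A reader who takes 9.5% as the incidence at which 2000 recruits deliver 90% power would be misled. If early preterm birth turned out to be exactly that common, the study would still fall short of 189 usable cases. Anyone monitoring event rates against 9.5% would conclude too early that the target is secure.

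**Working it through.** **Inputs from the article.** 2000 recruits; 189 cases; 9.5%; 80% against 70% sensitivity; 90% power; a 70% spontaneous/PPROM share of preterm births in general.

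**Assumptions.** The article does not state the significance level, sidedness or type of test. I use a one-sample test of a proportion, two-sided 5%, null 80%, because this reproduces 189. The article gives no loss fraction, so I use 10%, 20% and 30% as an illustrative range, applied equally to cases and non-cases. The 70% share is a background figure, not specific to births before 34 weeks or to these districts; applying it here is an assumption.

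**Step 1: reproduce the stated figure.**

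n = [(1.960 × √(0.8 × 0.2) + 1.2816 × √(0.7 × 0.3)) / 0.10]² = [(0.7840 + 0.5873) / 0.10]² = 188.04, rounded up to 189.

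Power with n cases = Φ[(0.10 × √n − 0.7840) / 0.4583]. At n = 189 this is Φ(1.289) = 90.1%. The claim reproduces.

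**Step 2: find the denominator.** 189/2000 = 9.45%, which rounds to the stated 9.5%. Likewise 460/2000 = 23%. Both figures are taken over all recruits.

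**Step 3: hold the incidence at 189/2000 and remove births that cannot be evaluated.**

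| Meaning of preterm birth before 34 weeks | Assumed loss | Evaluable cases | Power |
|---|---|---|---|
| Spontaneous/PPROM only | 10% | 189 × 0.9 = 170 | 87% |
| | 20% | 189 × 0.8 = 151 | 83% |
| | 30% | 189 × 0.7 = 132 | 79% |
| All preterm births, 70% spontaneous | none | 189 × 0.7 = 132 | 79% |
| | 10% | 132.3 × 0.9 = 119 | 75% |
| | 20% | 132.3 × 0.8 = 106 | 70% |
| | 30% | 132.3 × 0.7 = 93 | 65% |

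**Step 4: find the incidence that would deliver 189 evaluable cases from 2000 recruits.**

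- Spontaneous/PPROM incidence among evaluable women: 189/1800 = 10.5%, 189/1600 = 11.8% and 189/1400 = 13.5% at 10%, 20% and 30% loss.
- All-cause incidence, before any other loss, if 70% are spontaneous: 189/0.70 = 270, and 270/2000 = 13.5%. That is 270/460 = 59% of the births expected before 37 weeks, against 189/460 = 41% as the article stands.

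**The case against.** The sentence is conditional and follows an admission that the local incidence is unknown. The 189 is a requirement, and 9.5% looks like that requirement divided by 2000 rather than a forecast. A reader might infer that the power calculation is wrong, or that true power is 79%. The document supports neither: 189 evaluable cases do give 90%, and the eventual case count is unknown. What survives is narrower. The incidence printed beside the requirement does not deliver it for the stated endpoint and analysable women.

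A reader might also infer that the 189 certainly includes iatrogenic births. Later in the same section the primary endpoint is itself called simply preterm birth before 34 weeks, so the phrase may be shorthand for the spontaneous/PPROM endpoint. Against that, the section uses the unqualified term for the 23% rate and names iatrogenic birth as a kind of preterm birth to be excluded. The wording does not settle the matter, so both readings are shown. Under either, cases fall below 189.

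The 70% share is weak evidence here. The article describes a setting with little routine intervention and poor facilities, which gives reason to doubt that 30% of early births would be iatrogenic. It is the only share the article gives, and the direction of the finding does not depend on it.

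Some losses may be small. The inclusion criteria list ultrasound dating as a recruitment criterion, which could mean that the 2000 are already dated. The visit sequence and the exit section point the other way. Contaminated samples may be recollected within 7 days where possible. A detailed attrition allowance may also stand in the full protocol. None of this makes the printed pairing of 189 with 9.5% of all recruits consistent with the exclusions in the same section.

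The training and validation split would reduce the cases per set further. That is a separate matter and no part of these figures.

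**Conclusion.** The point holds in this limited form: the arithmetic is sound, but 9.5% of 2000 recruits does not yield 189 evaluable primary-endpoint cases, so the 90% power is not delivered at that incidence.

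The direction follows from the article's own endpoint and exclusions. The size does not. If the phrase already means spontaneous/PPROM births, power is 87–79% under an assumed 10–30% loss; a loss of about 5% would cost little, leaving 88.7%. If it means all preterm births and the 70% share carries over, power is 79% before other losses and 75–65% after them. All figures use the whole cohort and the one-sample, two-sided 5%, null-80% test that reproduces 189.

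**What to change.** In Sample size and data analysis, and in the matching text under Study design:

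1. Define the target as 189 spontaneous/PPROM births before 34 weeks among ultrasound-dated singleton pregnancies with an evaluable saliva result.
2. State that 2000 is the number recruited and give the number expected to be evaluable.
3. Replace 9.5% with the incidence needed after expected losses. For spontaneous/PPROM births this is 10.5%, 11.8% or 13.5% at 10%, 20% or 30% loss. If an all-cause figure is preferred, it is 13.5% before losses, with the 70% share labelled as an assumption.
4. Give power over a range of evaluable case counts, for example those in the table above.
5. Make the label of the primary endpoint later in the same section agree with Study outcomes.

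The cost is rewording and a less favourable stated power. The correction does not itself require further recruitment.

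### The 90% power for the primary endpoint (birth before 34 weeks) counts all 189 cases, but the equal training/validation split leaves about 95 for validation and about 66% power

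*Protocol article*

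**What the plan says.** The sample size argument appears under Study design and again under Sample size and data analysis. For births before 37 weeks, the latter expects 460 cases from 2000 women and describes this as "providing ample power to predict PTB at this gestation and to use data for discovery and validation". For births before 34 weeks it says the incidence in the study districts is unknown and gives a conditional figure: "if 189 cases of PTB < 34 weeks’ are identified (9.5% incidence"; if so, "this would provide 90% power to distinguish 80% from 70% sensitivity". The tool is named: "Calculations were carried out in Stata version 13.1 using the command ‘sampsi". Neither the significance level nor the null value is given.

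Later in the same section the analysis is set out: "The data will be randomly split into training and validation sets, each containing the same number of cases", with cases defined at both 37 and 34 weeks. The training set then serves to choose rule-in and rule-out cut-offs from six fixed values. Sensitivity, specificity, predictive values and ROC areas are to be reported with 95% confidence intervals at the two chosen cut-offs. Both Study outcomes and the analysis text make birth before 34 weeks the primary endpoint.

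**The concern.** The power statement and the split concern the same cases. The stated incidence shows that 189 is a count over the whole cohort, so the 90% holds only if every case before 34 weeks contributes to the sensitivity estimate. Under the split, half of them are used to choose the cut-offs.

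The article mentions discovery and validation when it discusses the 460 cases before 37 weeks, and makes no such allowance for the primary endpoint. Yet the section says that it concentrates on sensitivity because that is the harder quantity to determine. The mismatch therefore falls on the quantity that the sample size was built around. A reader would expect validated sensitivity before 34 weeks to be known to within about 6 points, when the planned analysis gives about 8.

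**Working it through.** **Inputs from the protocol article.** 2000 women; 189 cases before 34 weeks; 460 cases before 37 weeks; sensitivities of 80% and 70%; 90% power; equal numbers of cases in the two sets.

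**Assumption.** Two-sided alpha of 5%. It is not stated and is inferred in step 1.

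**1. Reproduce the plan's figure.** For a one-sample test of a proportion with null p0 and true value p1:

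n = [(1.960 × √(p0(1−p0)) + 1.2816 × √(p1(1−p1))) / (p1−p0)]²

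With p0 = 0.80 and p1 = 0.70: n = [(1.960 × 0.4000 + 1.2816 × 0.4583) / 0.10]² = 188.04, rounded up to 189. This matches.

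The variants tried do not match:
- p0 = 0.70, p1 = 0.80, two-sided 5%: 199.03, so 200.
- One-sided 5%: 156 (null 80%) or 161 (null 70%).
- Two-sample comparison: 392 per group, or 412 with continuity correction.

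**2. Establish what 189 counts.** 189 / 2000 = 9.45%, the stated 9.5%. So 189 is the whole-cohort count. If 189 were the validation count, the cohort would need 2 × 189 = 378 cases before 34 weeks. That is 378 / 2000 = 18.9% incidence, and 378 / 460 = 82% of all the preterm births that the article expects.

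**3. Apply the split.** 189 / 2 = 94.5, so 94 or 95 cases per set.

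**4. Power on the same formula.**

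Power = Φ[(|p1−p0| × √n − 1.960 × √(p0(1−p0))) / √(p1(1−p1))]

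| Cases | Null 80%, truth 70% | Null 70%, truth 80% |
|---|---|---|
| 189 | 90.1% | 88.3% |
| 95 | 66.1% | 57.6% |
| 94 | 65.7% | 57.1% |

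For example, with 95 cases and null 80%: (0.10 × 9.747 − 0.7840) / 0.4583 = 0.416, and Φ(0.416) = 66.1%.

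**5. Precision.** The 95% half-width at 80% sensitivity is 1.96 × √(0.80 × 0.20 / n):
- n = 189: 5.7 points.
- n = 95: 8.0 points.
- n = 94: 8.1 points.

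**6. Sensitivity to lost cases.** The article excludes iatrogenic preterm births and missing or contaminated samples without quantifying them. If 189 is the count before these exclusions, and if 90%, 80% or 70% of cases are evaluable (an assumed range), the validation set holds about 85, 75 or 66 cases. Power with null 80% is then about 62%, 57% or 52%.

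**The case against.** Several points on the other side have force.

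- **No hypothesis test is prescribed.** The analysis text asks for estimates with 95% confidence intervals and gives no null value or success rule. A reader might infer that the study is set up to fail a test against 70%. The document does not support that. Power enters only through the sample size statement, and the firmer consequence is the wider interval. This stands.
- **Reporting from the validation set alone is not stated.** It is the natural reading of a training/validation split, but it remains an inference. Reporting from the training half or from pooled data would not rescue the 90% as a validated figure, because the cut-offs would have been chosen on some or all of the same women.
- **The 90% is conditional.** The article says the incidence is unknown and writes the case count as an assumption, so it does not promise 189 cases. This stands, but the mismatch remains when the condition is met.
- **The direction of the null is a small matter.** The wording about distinguishing 80% from 70% is neutral. At 189 cases the choice changes power only from 90.1% to 88.3%. A reader might conclude that 189 is itself a mistake for 200. The document does not support that either.
- **A random hold-out set is a legitimate design.** A reader might infer that the split is an error and must be replaced by resampling. It is a trade-off between efficiency and a separate validation set, and the sponsor may keep it.

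**Conclusion.** The point holds as a mismatch between two statements in the same section. The 90% is correct arithmetic for 189 cases, but it does not describe the validation half that the analysis creates. The like-for-like figure there is about 66%, or about 57% if the aim is to show that a truly 80% sensitive test exceeds 70%. The half-width at 80% sensitivity is about 8.1 points, against 5.7 with all cases.

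This rests on three things: two-sided 5%, inferred because it reproduces 189; validated performance coming from the validation set, inferred from the purpose of the split; and 189 evaluable cases actually occurring. If fewer are evaluable, power is lower still.

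The mismatch does not bias any estimate, and it does not show that enrolment must be doubled. What needs correcting is the power and precision claimed for the primary endpoint.

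**What to change.** Keep the 189-case assumption and amend the sample size text in both places where it appears:

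- Give power and 95% confidence interval width for about 95 validation cases before 34 weeks: about 66% with null 80% and truth 70%, or about 57% with null 70% and truth 80%; half-width about 8.1 points at 80% sensitivity.
- State the null value, alpha and sidedness.
- Say that the performance measures are reported from the validation set.

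Optionally, the sponsor could use all evaluable cases and correct for optimism by bootstrap or cross-validation, repeating the whole cut-off selection in each resample. That recovers most of the lost precision but gives up a separate hold-out set.

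The first route costs wording only, plus a less favourable stated power. The second also needs some programming. Neither needs more women.

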### Study design

A prospective observational cohort study to recruit 2000 pregnant women from the two districts of Madhya Pradesh (Fig. 1). The flow of participants through the study is shown in Fig. 2. Mapping was conducted by the field staff to identify areas that had comparable population density and somewhat comparable geographic size, with natural boundaries noted.

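### The only control group named, term deliveries, fits the <37-week endpoint but not the primary <34-week or the <30-week endpoint; applied literally it would overstate PPV

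*Protocol article*

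**What the plan says.** The Study outcomes section of the Protocol article states that "the primary endpoint will be spontaneous preterm birth or PPROM < 34 weeks", with birth before 37 and before 30 weeks as secondary endpoints. The design is a cohort: "A prospective observational cohort study to recruit 2000 pregnant women".

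The section Sample size and data analysis divides the analysed women at random into two sets and describes the make-up of these sets as "each containing the same number of cases (premature deliveries before 37 and 34 weeks) and controls (term deliveries". One set serves to choose a rule-in and a rule-out cut-off. Later in the same paragraph, the plan promises that "measures of test performance (sensitivity, specificity, predictive values and ROC areas) will be produced with 95% confidence intervals". These measures are to be given for both chosen cut-offs against birth before 34 weeks, and also for the <37-week and <30-week endpoints. This accuracy sentence opens with "Following STARD guidelines" and names no non-case group of its own.

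For the numbers, the section expects that "recruitment of 2000 women would potentially identify 460 preterm deliveries" before 37 weeks. It bases power on 189 births before 34 weeks, and says that the incidence of such births in the two districts is not known.

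**The concern.** For a yes/no endpoint at 34 weeks, every analysed woman who passes that threshold undelivered is a non-case, whether she delivers at 35 or at 40 weeks. Term deliveries are the right complement of birth before 37 weeks. They are not the complement of birth before 34 weeks, where births at 34-36 weeks are missing, nor of birth before 30 weeks, where births at 30-36 weeks are missing.

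If the stated controls are carried into the <34-week tables, the comparison becomes early preterm against term, with the middle taken out. PPV then describes a population from which some of the women who would be tested in practice have been removed. This matters because the study's stated purpose is to support introducing the test in the community, where pregnancies ending at 34-36 weeks cannot be set aside in advance. The same sets also choose the cut-offs, so the mismatch could affect the thresholds as well as the reported accuracy.

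**Working it through.** **The plan's own figure.** The 189 cases come from a one-sample comparison of sensitivities, 80% against 70%, with 90% power. Two-sided 5% is assumed, since the article does not state it.

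n = [(1.96 × √(0.8 × 0.2) + 1.2816 × √(0.7 × 0.3)) / 0.10]² = 188.04, rounded up to 189.

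The figure reproduces. It concerns sensitivity only, so it does not depend on who the controls are.

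**Inputs.**
- 2000 women, 460 births before 37 weeks, and 189 before 34 weeks (a conditional figure): Sample size and data analysis.
- Sensitivity 80%: the value used in the power statement.
- Specificity among term births 88%: an illustrative midpoint of the 86-90% that the Background cites from two earlier studies. The Background does not say that those studies used term controls.
- Specificity *s* among 34-36-week births: not in the article. Assumed at 88% (no different from term), 80% and 60%.

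**Counts.**
- Births at 34-36 weeks: 460 - 189 = 271.
- Term births: 2000 - 460 = 1540.
- Non-cases for the <34-week endpoint: 271 + 1540 = 1811. Share not at term: 271/1811 = 15.0%.
- Prevalence: 189/2000 = 9.45% in the whole cohort; 189/(189 + 1540) = 10.9% with term-only controls.

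**Accuracy.** True positives = 0.80 × 189 = 151.2; false negatives = 37.8. False positives among term births = 0.12 × 1540 = 184.8; true negatives among term births = 1355.2.

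- Specificity = (1355.2 + 271*s*)/1811
- PPV = 151.2/[151.2 + 184.8 + 271(1 - *s*)]
- NPV = (1355.2 + 271*s*)/(1355.2 + 271*s* + 37.8)
- With term-only controls, the terms in 271 drop out.

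| Non-cases used | Specificity | PPV | NPV |
|---|---|---|---|
| Term only | 88.0% | 45.0% | 97.3% |
| All ≥34 weeks, *s* = 88% | 88.0% | 41.0% | 97.7% |
| All ≥34 weeks, *s* = 80% | 86.8% | 38.7% | 97.7% |
| All ≥34 weeks, *s* = 60% | 83.8% | 34.0% | 97.6% |

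The 4-point gap in PPV at equal specificity comes from the prevalence shift alone. It changes little across the cited range. At 86% in both groups, PPV is 151.2/366.8 = 41.2% term-only against 151.2/404.7 = 37.4%. At 90%, it is 151.2/305.2 = 49.5% against 151.2/332.3 = 45.5%.

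For the <30-week endpoint the article gives no incidence, so no equivalent figure can be worked out. The group left out would be births at 30-36 weeks, which contains the 34-36-week births.

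**The case against.** The best reply is that the sentence describes how the split is balanced, not how the two-by-two tables are built. Births at 34-36 weeks are births before 37 weeks, so they are present in both sets. Equal numbers of <37-week births, <34-week births and term births in each half already fix the three gestation bands. The list of additional exclusions in the same section does not include late preterm birth. The accuracy sentence, written under STARD, sets no restriction to term controls, and endpoint-specific definitions may sit in an analysis plan that is not shown.

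Most of this stands. A reader might infer that the plan drops 34-36-week births from the primary analysis; no text says so. What remains is that the article does name a control group, that it is the only one named, and that it does not fit the primary endpoint. A stated definition that is wrong for the endpoint differs from a detail left for later, and nothing else in the article assigns these women as <34-week non-cases.

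Two further inferences are tempting and do not hold. One is that all predictive values would be inflated. Leaving out 34-36-week births removes true negatives and keeps every false negative, so NPV falls slightly. The other is that specificity must be inflated. With the same positive rate at 34-36 weeks as at term, the effect on specificity is nil. A higher rate is plausible, because the plan also tests low progesterone as a predictor of birth before 37 weeks, but the article does not quantify it.

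**Conclusion.** The point holds as a mismatch between the stated control group and two of the three gestational endpoints, including the primary one. It does not hold as a finding that late preterm births are excluded.

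If the definition is applied literally to the <34-week analysis, PPV would be overstated by about 4 points with equal specificity in the two groups. With specificity of 80% down to 60% at 34-36 weeks, the overstatement is 6 to 11 points (45.0% against 38.7% and 34.0%). Under that same assumption specificity would be overstated by about 1 to 4 points. NPV would be understated by about 0.3 to 0.4 points.

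These sizes rest on the conditional 189 and the projected 460. They take all 2000 women as analysed, before exclusions such as iatrogenic preterm birth or a missing saliva sample, and will change with the true <34-week incidence. The direction for PPV does not depend on the assumed specificity at 34-36 weeks, provided that at least some of those women test positive. The sample size and the <37-week analysis are unaffected.

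**What to change.** Add one sentence to Sample size and data analysis: for each endpoint, the non-cases are all eligible analysed women still undelivered at that threshold (34+0, 37+0 and 30+0 weeks respectively), and this definition is used both for choosing the cut-offs in the training set and for estimating accuracy in the validation set. State the balance of the split as three bands (<34, 34-36 and ≥37 weeks), and keep all three in both sets and in every two-by-two table.

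No new data are needed and the sample size does not change. The cost is that the reported PPV, and possibly specificity, will be slightly less favourable than against term births alone. If the authors already intend this analysis, the change only makes the text agree with it.
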